## 13 INFORMED CONSENT PROCESS

- ☐ The requirement for informed consent has been waived (i.e., not required by law OR waived by IRB/REC/METC). Upload waiver if available.
- ☒ Written informed consent will be obtained from adult participants
- ☐ Assent will be obtained from children/minors
- ☐ Parental permission will be obtained when children are participating
- ☐ Surrogate consent will be obtained when participants lack decisional capacity
- ☐ Deferred consent will be obtained [e.g., emergency research]
- ☐ Click-through consent will be obtained [Internet/app-based research]
- ☐ Implied consent [i.e., consent through action such as taking a test]

### 13.1 Consent Process

Study participation is voluntary. Potential subjects, are given the most current ICBE/IRB/METC-approved consent form to read. They will be provided ample time (at least 2 weeks) for review and an opportunity to ask questions about the study.

If they agree to participate, they will sign the consent form and be given a copy of the signed document for their records. Each of these actions/steps will be documented. Only after Informed Consent has been obtained, may the remaining study procedures begin.

#### Eligibility process

After patients have signed up at the Obesity center, they undergo a screening to check if they are eligible for bariatric surgery. During this screening the nurse will also check inclusion criteria for the PEACH trial and, if eligible, will make a note about this in the electronic patient record. After screening, patients have a 'commitment' appointment. At this time patients will individually receive information about the study from a researcher who is not directly involved in the surgery or direct care of the patient. At least 2 weeks after this, if patients have been approved for surgery, they will have an appointment with the researcher who will check inclusion criteria and sign informed consent.

|                                                                                                                    |              |                         |                  |                    |
|--------------------------------------------------------------------------------------------------------------------|--------------|-------------------------|------------------|--------------------|
| Title: Clinical Investigation Plan                                                                                 |              | Author: [name] |                  | Philips restricted |
| DocID: ICBE-2-36455                                                                                                | Version: 3.0 | Date: 2020-DEC-08       | Status: Approved | Page: 37 of 44     |
| This document is based on Philips Research Template: Clinical Investigation Plan, ID: QR-TEM-57, Date: 2019-Mar-21 |              |                         |                  |                    |

[figure not shown]

## 13.2 New Information about the Study

Any new information about the study that may affect a consented subject's decision to be in the study (e.g., changed procedures, safety, etc.), will be communicated in a timely manner. Depending on the nature of the new information, subjects who have completed the study may or may not be informed, documenting the decision and justification as well as any activities for informing completed subjects. Additionally, the approving IRB/METC and/or regulatory authority will also be informed.

The currently approved Consent Form will be updated and submitted to the ICBE and approving IRB/METC and/or regulatory authority for review and approval. Active subjects will be re-consented, following the above process, with the newly-approved consent form.

## 14 ADVERSE EVENTS AND DEVICE DEFICIENCIES

### Definitions

Adverse events and adverse device effects, device deficiencies and serious adverse events and serious adverse effects and, unanticipated serious adverse device effects are defined in the table below:

|                                                                                                                    |              |                         |                  |                    |
|--------------------------------------------------------------------------------------------------------------------|--------------|-------------------------|------------------|--------------------|
| Title: Clinical Investigation Plan                                                                                 |              | Author: [name] |                  | Philips restricted |
| DocID: ICBE-2-36455                                                                                                | Version: 3.0 | Date: 2020-DEC-08       | Status: Approved | Page: 38 of 44     |
| This document is based on Philips Research Template: Clinical Investigation Plan, ID: QR-TEM-57, Date: 2019-Mar-21 |              |                         |                  |                    |

| Definition                          | Description                                                                                                                                                                                                                                                                                                                                                                                                                                                                                                                                                                                                                                                                                                                                                                                                                                                                 |
|--------------------------------------------|------------------------------------------------------------------------------------------------------------------------------------------------------------------------------------------------------------------------------------------------------------------------------------------------------------------------------------------------------------------------------------------------------------------------------------------------------------------------------------------------------------------------------------------------------------------------------------------------------------------------------------------------------------------------------------------------------------------------------------------------------------------------------------------------------------------------------------------------------------------------------------|
| Adverse Event (AE)                         | 
Any untoward medical occurrence, unintended disease or injury, or untoward clinical signs (including abnormal laboratory findings) in subjects, users or other persons, whether or not related to the investigational medical device
 
NOTE 1 This definition includes events related to the investigational medical device or the comparator.
 
NOTE 2 This definition includes events related to the procedures involved.
 
NOTE 3 For users or other persons, this definition is restricted to events related to investigational medical devices.
                                                                                                                                                                                                                                                                                                         |
| Adverse Device Effect (ADE)                | 
Adverse event related to the use of an investigational medical device
 
NOTE 1 This definition includes events related to the investigational medical device or the comparator.
 
NOTE 2 This definition includes events related to the procedures involved.
 
NOTE 3 For users or other persons, this definition is restricted to events related to investigational medical devices.
                                                                                                                                                                                                                                                                                                                                                                                                                                                                        |
| Serious Adverse Event (SAE)                | 
Adverse event that
 
 
a) led to death,
 
b) led to serious deterioration in the health of the subject, that either resulted in 
 
1) a life-threatening illness or injury, or
 
2) a permanent impairment of a body structure or a body function, or
 
3) in-patient or prolonged hospitalization, or
 
4) medical or surgical intervention to prevent life-threatening illness or injury or permanent impairment to a body structure or a body function,
 
 
 
c) led to foetal distress, foetal death or a congenital abnormality or birth defect
 
 
NOTE Planned hospitalization for a pre-existing condition, or a procedure required by the CIP, without serious deterioration in health, is not considered a serious adverse event.
 |
| Serious Adverse Device Effect (SADE)       | 
Adverse device effect that has resulted in any of the consequences characteristic of a serious adverse event or that might have led to any of these consequences if suitable action had not been taken or intervention had not been made or if circumstances had been less
                                                                                                                                                                                                                                                                                                                                                                                                                                                                                                                                                                                                  |
| Unanticipated Adverse Device Effect (UADE) | 
Serious adverse device effect which by its nature, incidence, severity or outcome has not been identified in the current version of the risk analysis report
 
NOTE Anticipated serious adverse device effect (ASADE) is an effect which by its nature, incidence, severity or outcome has been identified in the risk analysis report.
                                                                                                                                                                                                                                                                                                                                                                                                                                                                                                                                |

## Reportability

All adverse events shall be reported to the Study Manager. ADEs, SAEs, SADEs and USADEs shall be reported to the Q&R office as well ([[contact]](mailto:[contact])). The Director Q&R shall assess the ADEs, SAEs, SADEs and USADEs for reportability to Competent Authorities.

Gewijzigde v

|                                                                                                                    |              |                         |                  |                    |
|--------------------------------------------------------------------------------------------------------------------|--------------|-------------------------|------------------|--------------------|
| Title: Clinical Investigation Plan                                                                                 |              | Author: [name] |                  | Philips restricted |
| DocID: ICBE-2-36455                                                                                                | Version: 3.0 | Date: 2020-DEC-08       | Status: Approved | Page: 39 of 44     |
| This document is based on Philips Research Template: Clinical Investigation Plan, ID: QR-TEM-57, Date: 2019-Mar-21 |              |                         |                  |                    |

## Reporting process

Reporting shall include the date of the adverse event, research subject ID#, description of the adverse event, treatment, resolution, and assessment of both the seriousness and the relationship to the investigational device and study procedures.

## Timelines

The time period in which the principal investigator shall report all adverse events and device deficiencies to the sponsor and, where appropriate, to ECs and the regulatory authority, and the details of the process for reporting device deficiencies, are detailed in the table below.

| Category                                   | Report to Study Manager                                         | Report to Accredited Ethics Committee                                                              | Report to Q&R office
[contact]
[contact] or
[name]
[contact] (inform us after you send a fax) |
|--------------------------------------------|-----------------------------------------------------------------|----------------------------------------------------------------------------------------------------|------------------------------------------------------------------------------------------------------------------------------------------------------------------------------------------------------------|
|                                            | by
Principal Investigator                                    | by
Principal Investigator                                                                       | by
Principal Investigator
by Study Manager                                                                                                                                                           |
| Adverse Event (AE)                         | Periodic reporting to Sponsor
Periodic collection by Sponsor | As part of Sponsor's Clinical Investigation Report                                                 |                                                                                                                                                                                                            |
| Adverse Device Effect (ADE)                | Immediate, < 24 hr                                              | As part of Ethics Committee Reporting timelines
or
< 24 hr following instructions by Sponsor | Immediate, <24 hr                                                                                                                                                                                          |
| Serious Adverse Event (SAE)                |                                                                 | As part of Ethics Committee Reporting timelines
or
< 24 hr following instructions by Sponsor |                                                                                                                                                                                                            |
| Serious Adverse Device Effect (SADE)       |                                                                 | Immediate, < 48 hrs                                                                                |                                                                                                                                                                                                            |
| Unanticipated Adverse Device Effect (UADE) |                                                                 | As part of Ethics Committee Reporting timelines
or
< 24 hr following instructions by Sponsor |                                                                                                                                                                                                            |

|                                                                                                                    |              |                        |                  |                    |
|--------------------------------------------------------------------------------------------------------------------|--------------|------------------------|------------------|--------------------|
| Title: Clinical Investigation Plan                                                                                 |              | Author: [name] |                  | Philips restricted |
| DocID: ICBE-2-36455                                                                                                | Version: 3.0 | Date: 2020-DEC-08      | Status: Approved | Page: 40 of 44     |
| This document is based on Philips Research Template: Clinical Investigation Plan, ID: QR-TEM-57, Date: 2019-Mar-21 |              |                        |                  |                    |

Gewijzigde v

### Foreseeable adverse events and anticipated adverse device effects

No anticipated adverse device effects have been identified. However, since the study described here aims at detecting deterioration of health in patients post surgery, the following adverse events not associated with this study but with surgery in general are expected:

- Bleeding
- Anemia
- Anastomotic leakage
- Infection: wound, abdominal, pneumonia, urinary tract
- Dehydration
- Delayed gastric emptying
- Thrombosis: cerebral or cardiac infarction, intestinal ischemia, lung embolism

According to the Inspectie voor de Gezondheidszorg (Aanmeldingsformulier klinisch onderzoek met medisch hulpmiddel, Bijlage E 2017-07-14) these adverse events even if considered serious are not reportable since they are expected and described here as long as they do not lead to the suspension or termination of the trial or result in a change of the investigational product.

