| Anticipated adverse device effects                                                            | The only anticipated adverse device effect is an allergic reaction to the plaster used to locate the device on the skin of the patient. This is mitigated by excluding patients with known allergies to these kind of medical adhesives.                                                                                                                                                                                                                                                                 |
| Residual risks associated with investigational device [as identified in risk analysis report] | 
The residual risks associated with the devices and their potential interference with the clinical work flow have been identified, scored and mitigated. From the risk analysis it is concluded that the residual risks associated with the devices are acceptable.
 
The residual privacy risks associated with the study are that the devices with heart rate and respiratory rate data on it could come of and fall in the hands of unauthorized people.
                                   |
| Risks associated with participation in clinical investigation                                 | Risks for participating in this investigation have been identified, assessed and mitigated. The residual risks are detailed in the Risk management Summary Matrix and are all deemed acceptable. Though the patients undergo surgery with the associated risks of this procedure this is not part of the study and the study does not influence the surgery risks. Sending the patient home on the same day has been assessed in bariatric surgery in several studies and risks associated with this are |

|                                                                                                                    |              |                         |                  |                    |
|--------------------------------------------------------------------------------------------------------------------|--------------|-------------------------|------------------|--------------------|
| Title: Clinical Investigation Plan                                                                                 |              | Author: [name] |                  | Philips restricted |

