### Secondary hypotheses

- Patient satisfaction >6 points (on a scale of 1-10) is not significantly different between both groups
- Outpatient recovery after standard bariatric surgery with Healthdot monitoring is feasible based on evaluating recruitment rate (>60% of patients), adherence to protocol (>75% of patients), and the amount of missing data (<10%).
- False-positive notifications from the Healthdot system are lower than 10% of notifications per patient.
- Missed events (false negatives) i.e. there was no notification from the Healthdot system when the patient needed to go to the hospital, are lower than 5% of all notifications.
- Missed minor events occur less than five times per patient. Missed minor events are defined as when there was no notification from the Healthdot system and the patient contacted the hospital, but there was no need for the patient to visit the hospital.
- The outcome of patients who choose HD versus patients who were randomized to HD on a combined outcome measure as defined for the primary endpoint are the same.
- The number of adverse events is not significantly different in both groups.

|                                                                                                                    |              |                        |                  |                    |
|--------------------------------------------------------------------------------------------------------------------|--------------|------------------------|------------------|--------------------|
| Title: Clinical Investigation Plan                                                                                 |              | Author: [name] |                  | Philips restricted |
| DocID: ICBE-2-36455                                                                                                | Version: 3.0 | Date: 2020-DEC-08      | Status: Approved | Page: 21 of 44     |
| This document is based on Philips Research Template: Clinical Investigation Plan, ID: QR-TEM-57, Date: 2019-Mar-21 |              |                        |                  |                    |

- The amount of pain medication during day of surgery until evening in both groups is not significantly different.
- Clinical decisions made on basis of remote monitoring with the Healthdot system do not change in more than 5% of cases when information from a telephone consultation is also included in the decision making process.

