For each patient, the parameters mortality, severe postoperative complications (Clavien-Dindo IIIb or higher), readmission (at least one night in hospital), mild complications (Clavien-Dindo II and IIIa) and prolonged length of stay (3 days or more in hospital) within 30 days after primary surgery will be determined from the patient medical record by the principal investigator. Patient satisfaction will be obtained through a questionnaire at the end of the 8-day study period. Healthcare professional satisfaction will be obtained through questionnaires after all patients have completed the study. Percentage of missing data will be determined at the end of the study. False positive and false negative notifications from the Healthdot system will be noted by the healthcare professional that receives the notifications. Clinical decisions made based on the Healthdot system, that changed when information from a telephone consultation was also included, will be noted by the healthcare professional that makes the decisions. The costs will be estimated for each patient, based on the events that occurred as noted in the patient medical file. The principal investigator will retrieve this information from the patient medical file. Costs calculation will include hospital stay, additional contacts, re-admission-hospital stay for mild complications (less than Clavien Dindo 3, like superficial woundinfection, dehydration, pain or worryiness patient).

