On day 3-8 the physician will check the Healthdot dashboard daily. The physician may decide to have a telephone consultation, e.g. when the Healthdot dashboard flags an event. If the physician will determine that additional action is needed (e.g. based on the information on the dashboard, or when the patient calls), in the absence of an indication from the Healthdot, such an event will be viewed as a false negative. It will be retrospectively assessed, based on the patient medical record, if false negative events have occurred. For all events flagged in the Healthdot dashboard, the physician will record whether it was a false positive notification or a true positive notification in the eCRF.

Patients in the regular recovery group will be released from hospital on the discretion of a nurse under supervision of the physician the day after surgery. For these patients no appointments outside of the regular protocol are planned.

*Table 1: Overview of protocol activities in the hospital for the two patient groups, and the differences*

| Protocol Activity for patient group
"Outpatient recovery"                                                                                                                                                                                                                                                   | Protocol Activity for patient group
"Regular recovery"                                                                                                                                                                                                                                                      | Differences                                                                                                                                        |

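### Sections 4 and 14 disagree on anticipated adverse device effects, and section 14 classes expected complications as unrelated to the study with no exception for one the Healthdot failed to flag

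*Protocol*

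**What the plan says.** On anticipated device effects, section 4 (Risks and benefits assessment) says: "The only anticipated adverse device effect is an allergic reaction to the plaster used to locate the device on the skin of the patient". Section 14 (Foreseeable adverse events and anticipated adverse device effects) says: "No anticipated adverse device effects have been identified".

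The same part of section 14 then lists bleeding, anemia, anastomotic leakage, infection, dehydration, delayed gastric emptying and thrombosis, introduced by "the following adverse events not associated with this study but with surgery in general are expected". Citing a form of the Dutch inspectorate, it concludes that "these adverse events even if considered serious are not reportable since they are expected and described here". The only exceptions are events that lead to suspension or termination of the trial or to a change in the product.

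On missed events, section 5 (Secondary hypotheses) defines a false negative as a case where "there was no notification from the Healthdot system when the patient needed to go to the hospital" and sets a limit of 5% of all notifications. Section 6.1 says: "False positive and false negative notifications from the Healthdot system will be noted by the healthcare professional that receives the notifications". Section 6.4 (Discharge from hospital) counts as a false negative any case where the physician finds action necessary without an indication from the Healthdot, and adds: "It will be retrospectively assessed, based on the patient medical record, if false negative events have occurred".

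On reporting, section 14 (Definitions) makes an adverse device effect (ADE) any adverse event related to use of the device, with the note "This definition includes events related to the procedures involved". Under Reportability and Reporting process, all adverse events go to the Study Manager; ADEs, serious adverse events (SAEs) and serious device effects also go to the Q&R office. Each report assesses relationship to the device and to the study procedures.

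**The concern.** There are two separate defects.

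The first is a plain contradiction. An investigator who consults the protocol to see which device effects are anticipated finds one in section 4 and none in section 14.

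The second concerns the failure that matters most in this design. Section 3 says the main reason for the night in hospital is to detect short-term complications such as bleeding, and presents remote monitoring as what makes earlier discharge possible. If a group A patient bleeds at home and the Healthdot gives no notification, the obvious question is whether harm followed from delayed detection, and so whether the event is related to use of the device. Section 14 has already put bleeding among events unconnected with the study. An investigator who follows that wording has a written reason to record the event as surgical and go no further.

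What is at stake is classification and timing. Under Timelines, an adverse event is reported to the Study Manager periodically, while an ADE is reported immediately, within 24 hours. Section 6.3 ends a subject's participation when an SAE may reasonably have been caused by the device. Both depend on a relatedness judgement that section 14 steers in one direction, while further patients go home with the same prototype.

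**Working it through.** No arithmetic applies, so the passages are set side by side.

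1. **Count of anticipated ADEs.** Section 4 gives one and section 14 gives none. Both are current text in the same version, so they cannot both stand.

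2. **Does resolving step 1 settle missed notifications?** No. Section 4 does not list a missed notification either. Making the two sections agree on plaster allergy would leave the handling of missed events as it is. The two defects are independent and need separate changes.

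3. **Is a missed notification foreseeable from the protocol?** Yes. Section 5 defines it and sets a threshold. Section 6.4 says the dashboard flags events with a heart rate above a preset threshold, so a complication without a raised heart rate may produce no flag.

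4. **Can the resulting harm be an ADE?** Yes. The definition asks only whether the event is related to use of the device. It does not require that the effect was listed in advance.

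5. **What does section 14 say of the complications concerned?** It declares the listed complications unconnected with the study as a class. Its exceptions are suspension, termination or a product change. An event that the device failed to flag is not among them.

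6. **Do these events still reach someone?** Yes. All adverse events reach the Study Manager and SAEs also reach the Q&R office, with a relatedness assessment. The statement on non-reportability cites the inspectorate's form and sits beside these internal routes; it does not cancel them.

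7. **Is the missed notification linked to that assessment?** Not in the text. Sections 6.1 and 6.4 collect false negatives as endpoint data and do not refer to section 14. The required contents of a report (date, subject, description, treatment, resolution, seriousness, relationship) do not include whether a notification had been given.

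Steps 4 and 6 show that the route exists. Steps 5 and 7 show that nothing directs a missed notification into it, and that the wording of section 14 argues against doing so.

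**The case against.** The strongest case on the other side is that the reporting system already covers this. An unlisted effect can still be an ADE. Relatedness must be assessed in every report. A missed complication that needs admission would ordinarily be an SAE and reach the Q&R office whatever its label. Section 6.3 presupposes a device-causality judgement on SAEs. False negatives are noted during monitoring by the professional receiving notifications, and the retrospective review can be read as a completeness check. All of this stands. A reader might infer that a missed event has no route into device-effect reporting, or is recognised only afterwards; the documents do not support either reading.

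Two further inferences also fail. One is that the missed-event hypothesis contradicts section 14. It is a performance hypothesis and calls nothing an ADE. The other is that a serious skin reaction would be anticipated under section 4 and unanticipated under section 14. The definition of an unanticipated effect refers to the risk analysis report, not to either section, so the contradiction has no shown effect on that classification.

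It can also be said that the risk analysis report and the risk management matrix, which are not at hand, may address missed detection. They may, but they would not remove the conflict between sections 4 and 14, or the unqualified wording of section 14 that the investigator reads.

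What survives the objection is narrower: a relatedness assessment is required, but it is not informed by the one fact that matters for this device, and the protocol suggests the answer in advance.

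**Conclusion.** The point holds in two parts. Sections 4 and 14 contradict each other on anticipated ADEs. Separately, section 14 pre-classifies the expected complications as unrelated and not reportable, without excepting one that the Healthdot failed to flag in a patient sent home, and no stated rule brings a missing notification into the relatedness assessment. The change should be made, because it is cheap and bears on safety. The primary composite is unaffected, since its components do not depend on device relatedness.

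The size cannot be derived. A reader might start from the hospital's 95% textbook outcome, giving 100 × 0.05 = 5 events in group A, or add the 7-point margin, giving 100 × 0.12 = 12, and then apply an assumed detection rate of 50% to 80%. That yields 5 × 0.2 to 5 × 0.5 = 1.0 to 2.5 unflagged events, or 12 × 0.2 to 12 × 0.5 = 2.4 to 6.0. These figures are not evidence. The protocol gives no detection rate, the composite covers 30 days while the device is worn for 8, and it includes prolonged stay. An unflagged event is also not device harm unless the missing notification contributed to it.

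The conclusion rests on the protocol text alone and assumes that no accompanying document qualifies section 14 on this point.

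**What to change.** Three changes to the text:

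- Reconcile the statement in section 14 with section 4, so that both give the same list of anticipated ADEs.
- State in section 14 that the wording on complications being unconnected with the study and not reportable does not apply to a group A event during Healthdot wear until its relationship to a missing or late notification has been assessed.
- Add one field to the adverse event report for group A events up to day 8: whether a notification had been given. Use it in the relatedness assessment under Reporting process, on the existing timelines of section 14.

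Classification as an ADE or serious ADE should stay with the investigator's causality judgement. Entering every unflagged hospital visit as a suspected device effect would override that judgement and would sweep in visits where no notification could be expected, such as a wound problem with a normal heart rate. The retrospective review in section 6.4 stays as a completeness check.

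The cost is a few sentences, one extra field and possibly a few more device-effect reports, whose number the protocol does not allow anyone to estimate.
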